**Figure 1 fig1:**
[figure not shown]
Flow chart of patient’s inclusion and experimental procedures. ^*^The PedsQL and VABS-II will be administered only at T0 and T2, while all other measures will be administered at all timepoints.

Each pair of patients will be randomly assigned to one of two groups (active vs. sham group) with an allocation ratio 1:1, through a computer-generated blocked randomization procedure conducted by independent personnel not directly involved in performing the intensive training. The patients and their parents, the personnel responsible for conducting the bimanual training and analyzing clinical data will be kept blind to the group allocation. Instead, the coordinator of the study and the personnel administering the tVNS will be “not blind.” With respect to the clinical assessment, the staff administering and scoring the scales will be blinded to group allocation. Questionnaire scores and neuropsychological tests will not contain personal information about the patients, who will be identified by an alphanumeric code. All records that contain names or other personal identifiers, such as informed consent forms, will be stored separately from study records identified by code number. In order to uphold the overall quality and credibility of the clinical trial, instances of code breaks should be limited to exceptional circumstances, where knowledge of the actual treatment is deemed absolutely necessary for the ongoing management of the patient. The intensive treatment will take place at the Scientific Institute, IRCCS E. Medea in Bosisio Parini (Lecco, Italy; study sponsor), Fondazione Mondino IRCCS in Pavia (Italy), and ASST Ospedali Civili in Brescia (Italy). The SPIRIT checklist used for protocol reporting can found in the Supplementary material.

## Patient selection

Male and female children and adolescents with a diagnosis of CP will be considered for eligibility if they are aged from 6 to 17 years. Inclusion criteria will comprise: the presence of clinical signs of unilateral or bilateral upper limb deficits, with a difference at least of 25% between the more affected and the less affected one at Box and Block test; a Magnetic Resonance Imaging confirmed diagnosis according to Surveillance of Cerebral Palsy (SCPE) criteria (37); MACS level I, II, III; Gross Motor Function Classification System level (GMFCS) I, II, III; Visual Function Classification System level (VFCS) between I, II, III; and IQ > 50. The exclusion criteria will include the presence of cochlear implant, cardiac pacemaker, ventriculoperitoneal shunt, neuro-stimulators, clips, fragments or metal splinters in the brain or skull except for titanium; treatments for spasticity or functional surgery of the upper limb in the previous 6 months or planned during the duration of the study, and uncontrolled epileptic seizures in the last 2 years. Before being included in the study, physicians will ensure thorough comprehension of the study’s purpose and design. The parents of the participants and each participant itself have to indicate their willingness to participate before being included.

## Outcome measures

The primary outcomes consist of two validated measures of manual dexterity, namely the Assisting Hand Assessment (AHA), and the Box and Block test (BBT), and a pc-administered, *ad-hoc* visuomotor task for the evaluation of manual visuomotor control. Secondary outcomes encompass a comprehensive assessment of motor skills, functional adaptation, and quality of life. The following paragraphs provide a detailed description of both primary and secondary outcomes (Figure 2).

**Figure 2 fig2:**
[figure not shown]
Schedule of enrolment, intervention, and assessment.

### Primary outcomes

#### Assisting hand assessment

This scale enables quantifying the assistance provided by the more affected hand to the less affected hand during bimanual activities. This observation-based, criterion-referenced assessment highlights a person’s typical performance, emphasizing practical functionality over maximal capacity, and serves as a reliable measure of change over time. The scale comprises 20 items, scored on a four-point Likert scale, from 1 to 4. The total score indicates how well the more affected hand is used as an assisting hand. A score of 20 means poor performance (the hand is not used as an assisting hand); a score of 80 means that the hand is used effectively. The results are converted for each of the three scales to logits by a Rasch analysis, on a 0–100 scale (with higher scores suggesting better use). This assessment has been shown to be responsive, reliable and valid for use in children with CP (38).

#### The box and block

This test is designed to measure manual dexterity. It is quick, simple, and cost-effective. It involves a box with a partition in the middle placed on a table, with a total of 150 blocks on one side of the partition. The score of the test is given by the number of blocks transported within a minute (39, 40) and it is performed with both the less and the more affected hands. The BBT provides a reliable and objective measurement of manual dexterity, making it valuable for evaluating functional outcomes and monitoring progress in rehabilitation programs over a short period of time (41).

#### The visuomotor task

This is an *ad hoc* computer-based task for the evaluation of manual visuomotor control. It involves a mouse click-and-drag operation where an object appears at the center of the screen. The objective is to drag and drop the object to the location indicated by a previously presented arrow, pointing toward a target object within a configuration of objects. Participants are required to focus on the direction of the arrow, swiftly and accurately moving the central object to its designated target location, by using a mouse with the less affected hand. This task enables the measurement of movement time (MT, in milliseconds; consisting in the time necessary to move the object in the target position); precision error (calculated as the distance, in pixels between the drop position of the object and the actual target position); the proportion of overtime errors (the percentage of trials in which responses are too slow). Smaller values of Movement time, Precision error and overtime errors indicate better performance.

### Secondary outcomes

#### The children’s hand-use experience questionnaire

The CHEQ is a parent report questionnaire that includes 27 bimanual activities (for example Cut up a pancake or other food easy to cut upon the plate). Each activity is rated on three scales measuring: (i) the perceived efficacy of the activity (“How do you think the child’s hand works?”) from 1 (meaning Bad/not used hand) to 4 (meaning Good efficacy); (ii) the amount of assistance and the time needed to perform the activity (“How much time does your child need to do the whole task, compared to peers?) from 1 (meaning Considerably longer) to 4 (meaning Equally long time compared to other peers); and (iii) child’s satisfaction with their performance (“Is your child bothered by his/her reduced hand/arm function during this activity?”) from 1 (corresponding to “It bothers him/her a lot”) to 4 (corresponding to “It does not bother him/her at all”). The questionnaire provides a result corresponding to the summary of the ratings. The results are converted for each of the three scales to logits by a Rasch analysis (42), on a 0–100 scale (with higher scores suggesting better performance/satisfaction).

#### The Canadian occupational performance measure

The COPM is a client-centered, semi-structured interview used in occupational therapy to identify the problems experienced by the patients. This interview engages the patient in recognizing daily occupations of importance that he/she wants to do, needs to do, or is expected to do but is unable to accomplish. Upon the identification of the problems experienced in a patient’s everyday-life activities, the child is asked to rate the importance of each activity in his/her life through a 10-point rating scale and then to select up to five problems to be addressed during the intervention. Lastly, the patient is asked to rate on a 10-point scale his/her own level of performance and satisfaction in performing that activity for each of the five problems (from 0, low performance or low satisfaction, to 10, high performance or high satisfaction) (43).

#### The Melbourne assessment-2

This scale allows evaluating the unimanual performance of both the more and less affected hand. It measures four elements of upper limb movement quality: movement range, accuracy, dexterity, and fluency. It consists of 14 test items that require children to interact (by reaching, grasping, releasing, and manipulating) with simple objects. Movement elements are scored on a three-, four-, or five-point scale according to specific criteria. Scores are arranged into the four sub-scales (movement range, accuracy, dexterity, and fluency) according to the element of movement being rated. A child’s total raw score for each sub-scale is converted to a percentage of the maximum possible score for that sub-scale, with higher scores indicating better performance. It is a valid and reliable measure for the assessment of the quality of upper limb movements in children with neurological conditions (44).

#### Gross motor function measure

It is a standardized observational tool used by healthcare professionals to evaluate and quantify the gross motor abilities and limitations of children with CP. It assesses 66 motor skills across five dimensions: lying and rolling, sitting, crawling and kneeling, standing, and walking, running, and jumping. Each skill is scored on a four-point scale, ranging from 0 (does not initiate) to 3 (performs fully). Particularly advantageous in time-limited clinical settings, the GMFM-66 remains a reliable and valid tool for evaluating gross motor skills, providing clinicians with essential information about patients’ capacities and tracks their progress effectively (45).

#### The Vineland adaptive behavior scale version 2

This is a tool designed to assess adaptive behavior in individuals from birth to age 90. It assesses 11 subdomains of adaptive behavior grouped into four domains: Communication, Daily Living Skills, Socialization, and Motor Skills. The sums of sub-dimension scores are standardized into domain standard scores. Sums of the domain standard scores are then standardized into the Adaptive Behavior Composite score ranging from 20 to 160 (mean = 100; standard deviation = 15). It has a proven track record of application in the evaluation of children with CP (46).

#### The pediatric quality of life inventory (cerebral palsy module)

The PedsQL is a widely employed, brief, and standardized self-reporting tool for assessing health-related quality of life in children and young individuals. The measure can be completed by parents (the Proxy Report) as well as by children and young people (the Self-Report), with versions available for children and young people with CP aged 5–7, 8–12, and 13–18 years old. Parent-rated versions are available for children aged 2–4, 5–7, 8–12, and 13–18 years old. The versions from 5 to 18 years comprise 35 items comprising seven dimensions: Daily Activities; School Activities; Movement and Balance; Pain and Hurt; Fatigue; Eating Activities; and Speech and Communication. For each item, consisting in everyday life action, it is required to indicate how much of a problem each item has been in the past month with response options from 0 (never a problem) to 4 (almost always a problem). The items are reverse scored and transformed to a 0–100 scale, with higher scores indicating better health-related quality of life. The PedsQL serves as a valuable resource for healthcare professionals in clinical settings, facilitating the assessment of various aspects of health-related quality of life in pediatric populations, including children with CP (47).

### Safety and tolerability measures of tVNS

Cardiovascular parameters such as capillary saturation of O2 (SpO2) and heart rate (HR) will be measured during a 2-min rest condition. For HR, the stimulation will be interrupted in case of values lower than 70 or higher than 120 beats per minutes (bpm) in 6–12 years old children and lower than 60 or higher than 100 bpm in 12–17 years old adolescents. Analogously, the stimulation will be interrupted for SpO2 values lower than 93%. These parameters will be checked in the first 2 min, and after 20 and 75 min of stimulation. Furthermore, potential skin irritations will be assessed through visual inspection during each session, before and after the application of tVNS, examining the skin at the electrode placement site for signs of redness, swelling, or rash.

The tolerability will be assessed through Visual Analog Scale by asking the level of discomfort experienced during the stimulation, and to rate on Child-friendly Likert scales the intensity of the following sensations: itching, pain, burning, heat, pinching, iron taste, and fatigue, among others. For each sensation the patients will be asked to express a value of perception strength that ranges from 0 (absence) to 4 (strong). Higher values will suggest stronger discomfort. Moreover, the questionnaire includes a final open-ended question to inquire about any other potential side effects they may have experienced during the stimulation. These measurements will be taken after the end of each stimulation session.

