The overall RCT will be structured as follows. In the first session, prior to the beginning of the training (T0), the RCT will include the administration of all clinical assessment measures and the patients will be asked to perform for 10 min an *ad-hoc* computer based Visuomotor task (please refer to the outcome sessions for more a detailed description). Then, patients will undergo the 10-day treatment. For each training day, the treatment will last 3 h. During the first 75 min of treatment, the active or sham tVNS (according to group allocation) will be delivered. Before starting, 20 min after and soon after the end of the stimulation, the vital parameters will be checked. After the end of the stimulation, patients will be also asked to rate the sensations experienced during the stimulation through Visual Analog Scales and through child-friendly Likert scales. Then, they will continue the training for the remaining session time without stimulation. Soon after the end of all the training sessions, patients will carry the T1 evaluation. As for the T0 session, this session will include the administration of the clinical assessment measures and the execution for 10 min of the Visuomotor task. Three months after the end of the training (T2), the follow up assessment will be conducted, following the same exact procedure of T0.

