## Interventional methods

### Transcutaneous nerve vagus stimulation

Transcutaneous nerve vagus stimulation allows the non-invasive stimulation of the Vagus Nerve by delivering electrical pulses to the sensory afferent fibers of the auricular, thick-myelinated, branch of the vagus nerve in the outer ear. tVNS will be performed by using a CE-marked tVNS device tVNS®E (tVNS, technologies GMBH, Erlangen, Germany). It consists in a programmable stimulation unit connected to two titan ear electrodes that are mounted on a gel frame, allowing to generate and transfer electric impulses from the stimulation unit to the surface of the skin, where the electrodes are applied. The active tVNS will be applied through an active electrode placed on the cymba conchae (innervated by the auricular branch of the vagus nerve), while the sham stimulation will be administered by positioning the active electrode in correspondence of the earlobe, which is free of cutaneous vagus innervation (see Figure 3). Applying active stimulation in both the experimental and control groups, but at differently innervated positions of the ear skin, will allow for sham-control stimulation without hindering blindness to stimulation condition. To avoid cardiac effects, the electrodes will be applied to the left ear. The stimulation intensity will be set based on the perceptual threshold of the participants, corresponding to the perceived intensity and below the perception of pain, in order to make the stimulation tolerable. The device’s stimulation intensity ranges from 0.1 to 5 mA for individuals aged 3 years and older. However, in the present project the stimulation intensity will be constrained to range from a minimum of 0.5 mA to a maximum of 3 mA, falling within the range used in previous tVNS studies with pediatric populations (49). This will limit the risk of any major side effects (e.g., skin irritation) despite any sensorial deficits that may blur participants’ sensitivity to stimulation. In any case, the stimulation will be interrupted if participants would not tolerate the stimulation at the lowest predefined intensity. The intensity of the stimulation will be gradually increased to reach the intensity of stimulation with a ramping-up phase of 30 s. In both active and sham conditions, on (28 s) and off (32 s) periods of stimulation will be alternated, with pulses delivered every 200–300 μs at a frequency of 25 Hz. These are the most common parameters applied in tVNS studies, as outlined in a recent review on parameters settings for neurological and psychiatric disorders (50), and they are the default parameters of the CE-marked tVNS device used in this study. The tVNS, sham or active, will be applied for the first 75 min of the training, every day of the treatment. Given the duty cycle of alternating on and off periods, participants will receive 35 min of stimulation over a 75-min period in each session. Discontinuation to interventions will be contemplated in case of serious adverse effects, withdrawal of consent or significant changes in the participant’s health status, such as the development of any contraindication to the stimulation, that make continuing the intervention unsafe or inappropriate.

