However, an aspect deserving discussion pertains to the tolerability and safety of the stimulation. In general, tVNS is well tolerated and safe in both the pediatric and adult populations. To reduce any possible risks, participants will be thoroughly screened against the defined exclusion criteria to minimize the risks associated with the application of the stimulation. Moreover, to reduce potential effects on the heart, the electrode will be applied to the left ear, whose stimulation does not exert arrhythmic effects (19). The stimulation intensity will be set based on the perceptual threshold of the participants, corresponding to the perceived intensity and below the perception of pain. Setting the intensity below the pain threshold may lead to inconsistent stimulation across participants, resulting in variable outcomes that challenge data interpretation. This constitutes the main limitation of this approach. However, it also helps prevent dropout due to discomfort and promotes adherence to the training regime. Response variability according to inter-individual differences in tVNS responses will be also considered in order to identify best responses to tVNS with respect for example to gender, age and clinical impairments. Even if all recommended procedures will be followed, unwanted side-effects could be experienced by participants. As reported by the systematic review of a total of 51 studies published between the 2007 to the 2017 and involving a total of 1,322 participants (62), the most common effects could include tactile sensations and skin irritation under the electrode. Other less common sensations could include headache, vertigo, nausea, and nasopharyngitis. Very few studies reported cardiac side effects, that were transient and asymptomatic and gastrointestinal side effects. In each case, the occurrence of side effects and the intensity of each sensation will be accurately checked and safety parameters (SpO2 and HR) will be monitored.

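### After minute 20, no scheduled heart-rate or oxygen-saturation reading can trigger the rule for interrupting stimulation

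*Protocol article*

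**What the plan says.** The section *Safety and tolerability measures of tVNS* sets a numeric interruption rule. For the younger band, "For HR, the stimulation will be interrupted in case of values lower than 70 or higher than 120 beats per minutes". For adolescents the limits are 60 and 100 bpm, and for all participants a saturation below 93% also interrupts. The readings are taken over 2 min at rest, and their timing is explicit: "These parameters will be checked in the first 2 min, and after 20 and 75 min of stimulation".

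The *Design* section gives nearly the same schedule: "Before starting, 20 min after and soon after the end of the stimulation, the vital parameters will be checked". I read its middle time as 20 min after the start, as the safety section confirms. The two sections differ only on the first reading, which comes before the start in one and in the first 2 min in the other.

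Both *Design* and *Transcutaneous nerve vagus stimulation* fix the length of exposure at 75 min: "The tVNS, sham or active, will be applied for the first 75 min of the training, every day of the treatment". The latter section also allows stopping for intolerance and states that "Discontinuation to interventions will be contemplated in case of serious adverse effects". On expected risk, the *Discussion* says: "Very few studies reported cardiac side effects, that were transient and asymptomatic".

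**The concern.** A rule that interrupts stimulation can act only on a reading taken while stimulation is running. The protocol has three readings. The last coincides with the planned end of tVNS in one section and follows it in the other. Followed exactly, the schedule leaves the rule inoperative for most of each session.

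No other scheduled assessment covers the interval. Skin is inspected before and after application, and sensations are rated once stimulation is over. Stopping for intolerance depends on the child noticing and reporting a problem. The article itself notes that sensory deficits may dull perception of the stimulation, and it admits children with an IQ just above 50. If cardiac effects are asymptomatic, complaints cannot stand in for a reading.

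What is at stake is the protection of children receiving a technique that the Abstract describes as untested in cerebral palsy. The completeness of the trial's safety record is also affected, because an excursion that begins after minute 20 and resolves before minute 75 would not be recorded.

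**Working it through.** **Inputs**

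- Stimulation per session: minute 0 to minute 75 (*Design*; *Transcutaneous nerve vagus stimulation*).
- Duty cycle: 28 s on, 32 s off; stated current time 35 min per session (*Transcutaneous nerve vagus stimulation*).
- Readings: first 2 min, 20 min, 75 min (*Safety and tolerability measures of tVNS*), or before the start, 20 min, soon after the end (*Design*).
- Training: 10 sessions of 3 h, 30 h in total; 44 participants.

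**Reproducing the stated figure.** Current time = 75 × 28/(28 + 32) = 35.0 min, which matches the article.

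**Which readings can interrupt?**

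| Reading | Safety section | Design section |
|---|---|---|
| First | during stimulation: yes | before the start: cannot interrupt |
| Second (20 min) | during stimulation: yes | during stimulation: yes |
| Third | at 75 min, the planned end: no | after the end: no |

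On either schedule the last actionable reading is at minute 20.

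**Length of the uncovered stretch**

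- Elapsed: 75 − 20 = 55 min; 55/75 = 73%.
- Current time: 55 × 28/60 = 25.7 of 35 min.
- Over 10 sessions: 550 of 750 min.

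**Alternative reading of the times.** Suppose 20 min of stimulation means 20 min of current. That reading would fall at 20 × 60/28 = 42.9 min elapsed, leaving 75 − 42.9 = 32.1 min uncovered (about 43% of the session). The 75-min reading cannot be meant this way, since it would need 75 × 60/28 = 160.7 min elapsed. The conclusion is the same, with a shorter stretch.

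**Effect of one added reading (elapsed time)**

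| Added at | Gaps before and after it | Current time after it |
|---|---|---|
| 45 min | 25 and 30 min | 30 × 28/60 = 14.0 min |
| 47.5 min | 27.5 and 27.5 min | 27.5 × 28/60 = 12.8 min |
| 50 min | 30 and 25 min | 25 × 28/60 = 11.7 min |

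The longest interval between readings falls from 55 min to 30 min or less.

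**The case against.** The strongest reply is that nothing in the schedule is false and no check frequency is required by the document. Every set of spot checks leaves gaps, and the proposed one still leaves 25 to 30 min. The expected risk is also low: the left ear is used, intensity is capped at 3 mA against a device maximum of 5 mA and kept below pain, and pacemakers are excluded. No increase in intensity is described after the 30 s ramp, so by minute 20 the child has had over 19 min at the set level.

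A transient excursion could be missed by one further 2-min reading. A sustained one would also show at 75 min, where it could inform later sessions. An extra reading after active play could stop stimulation because of exertion, particularly against the 100 bpm limit for adolescents. Finally, this is a condensed article, and it says in general terms that vital parameters are examined in each session and monitored.

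Much of this stands as a limit on the stakes. Late excursions are not shown to be likely, and the gain from the fix is earlier stopping within a session plus one more chance of detection. The cost in exertion-related stops cannot be sized from the document, although the 2-min rest condition reduces it and the same problem already exists at minute 20.

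The objection does not remove the mismatch. The times are stated explicitly in two sections, so this is not detail deferred to a fuller document, and the general remarks on monitoring add no time point. A 2-min resting reading is a discrete measurement, not continuous recording during play.

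**Conclusion.** The concern holds. As written, the heart-rate and saturation rule can act only up to minute 20 of a 75-min exposure. For 55 min per session (73%; 25.7 of 35 min of current) no scheduled reading can trigger it.

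The finding is limited to this numeric rule and to scheduled readings. Staff may take unscheduled ones, the intolerance and discontinuation provisions still apply, and the 75-min reading remains a valid end-of-exposure record. The figures assume that the stated times are elapsed minutes; on the alternative reading above, the gap is 32.1 min.

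The point merits correction because the rule exists to protect children and the remedy is cheap. It is a modest safety improvement, with no bearing on sample size, error rates, outcomes or analysis.

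**What to change.** Add at least one 2-min resting heart-rate and saturation reading between minutes 20 and 75, for example at minute 45 to 50, under the limits already stated. Keep the 75-min reading as the post-stimulation safety record. State that times are elapsed minutes from the start of stimulation. If the 20-min check is in fact meant as current time (minute 42.9), put the new reading about midway through what remains, at (42.9 + 75)/2 ≈ minute 59.

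The cost is one line of protocol text and one short pause per session using a measurement already in place:

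- Per child: 2 × 10 = 20 min of 30 × 60 = 1,800 training minutes, or 1.1%.
- Whole trial: 44 × 10 = 440 further readings.

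There are two caveats. Some readings raised by recent exertion may stop stimulation in either arm, as can already happen at minute 20. The fix also assumes that someone able to stop the device is at hand; the article does not say whether the staff administering tVNS stay throughout, so the protocol should say so.

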**Results:**

The results of this trial will assess whether tVNS can effectively boost the effects of an intensive two-week bimanual training, in improving manual dexterity in children and adolescents with cerebral palsy, ensuring safety and tolerability throughout the intervention period.

**Clinical trial registration**:  ClinicalTrials.gov, NCT06372028.

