Primary outcomes will include the following clinical measures: Assisting Hand Assessment (AHA), Box and Block Test (BBT), and performance at the Visuomotor task. Secondary outcomes will include the scores at the following tests: Children’s Hand Experience Questionnaire (CHEQ), Canadian Occupational Performance Measure (COPM), Gross Motor Function Measure (GMFM-66); Melbourne Assessment-2 (MA2) scale, Vineland Adaptive Behavior Scale Version 2 (VABS II), and Pediatric Quality of Life Inventory (PEDS-QL). Vital parameters (i.e., oxygen saturation, SpO2, and Heart Rate, HR) and the scores at the questionnaires assessing stimulation-induced sensations will be also checked to assess the safety and the tolerability of the stimulation. Lastly, the feasibility and the acceptability of the training will be assessed by considering, respectively, the number of patients completing the training/the number of sessions for each patient and the response to *ad-hoc* questionnaires for the patients and their parents. All primary and secondary outcomes will be collected at each time point, except for the PEDS-QL and VABS II, which will be administered only at T0 and T2. Furthermore, vital cardiovascular parameters and the questionnaires assessing stimulation-induced sensations will be examined during each stimulation session. The acceptability questionnaires will be administered only after the end of the training (T1) (see Figure 1).

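### Side-effect questions cover only the 75-minute stimulation window, so later-onset non-skin effects are not systematically elicited and the aim of safety throughout the intervention is met only in part

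*Protocol article*

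**What the plan says.** The Design section sets the order of each day. Stimulation runs for the first 75 minutes; when it ends, "patients will be also asked to rate the sensations experienced during the stimulation". After that, "Then, they will continue the training for the remaining session time without stimulation". The same section gives the timetable: "vital cardiovascular parameters and the questionnaires assessing stimulation-induced sensations will be examined during each stimulation session". It schedules no side-effect question at T1 or T2.

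The section on safety and tolerability measures fixes the wording. The visual analogue scale works by "asking the level of discomfort experienced during the stimulation". A list of sensations is rated from 0 to 4, and the questionnaire closes with "a final open-ended question to inquire about any other potential side effects they may have experienced during the stimulation". On timing: "These measurements will be taken after the end of each stimulation session". The respondent is the patient.

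Other checks reach further. Skin is inspected before as well as after each application. The Design section also has vital signs checked before stimulation starts, although the safety section puts the first check in the opening two minutes. The Interventional methods section contemplates discontinuation for serious adverse effects or a significant change in health. The Discussion promises careful checking of side effects, without giving a time window, schedule or respondent.

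The stated aim is wider than the questions. The abstract's Results paragraph speaks of "ensuring safety and tolerability throughout the intervention period", and the Highlights count proof of safety and tolerability in cerebral palsy among the trial's products. The Discussion warns: "Other less common sensations could include headache, vertigo, nausea, and nasopharyngitis".

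**The concern.** The period asked about and the moment of asking are stated choices, not details left out for brevity. Both confine the questions to the stimulation itself, while the safety aim covers two weeks.

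Several effects that the Discussion names need not begin while the current is on, and nasopharyngitis is hardly a sensation felt during stimulation. The exclusion criterion on epilepsy concerns uncontrolled seizures, so children with controlled epilepsy can enter, and no scheduled question would bring out a seizure at home. Participants can be as young as 6 or have an IQ just above 50, yet no parent is asked about side effects. Parents see the evenings and the weekend, and they already complete other forms in this trial.

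Two things are at stake. The comparison of active with sham would be well informed on acute sensations but would depend on unprompted reports for anything later. And a non-skin reaction that begins after one day's stimulation has no scheduled question before the next day's.

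**Working it through.** **Inputs.** From Design and Interventional methods: 75 min of stimulation at the start of each 3 h (180 min) session; 5 days a week for 2 weeks, so 10 sessions; on/off cycle 28 s/32 s; T1 one or two days after the last session. From Sample size calculation: 22 children per group. Assumed: sessions on weekdays, with one weekend between the two weeks.

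**The plan's own figures.** Current-on time per session: 75 × 28/(28 + 32) = 35 min, as stated. Total training: 10 × 3 h = 30 h, as stated.

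**Share of time asked about**, taking the whole 75 minutes as covered:
- Per session: 75/180 = 41.7%. The other 180 − 75 = 105 min follow the questionnaire.
- Over the course: 10 × 75 min = 750 min = 12.5 h of the 30 training hours.
- From the start of day 1 to the end of the session on calendar day 12: 11 × 24 h + 3 h = 267 h, and 12.5/267 = 4.7%.

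The last figure gives every hour equal weight. It describes the reach of the question; it is not an estimate of the share of events missed.

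**Who or what looks at each interval:**

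| Interval | Described check | Side-effect question |
|---|---|---|
| During stimulation (75 min) | Heart rate, SpO2 | Yes, on its ending |
| Rest of session (105 min) | Therapist present; skin and vital signs once, as stimulation ends | None |
| Evening, night, weekend | Skin and vital signs around the next start | None |
| Last session to T1 | None described | None |

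**What a clean result would show.** If none of the 22 active children reported an effect, the one-sided 95% upper bound on its rate would be 1 − 0.05^(1/22) = 12.7%. That bound would apply only to effects arising in the window asked about.

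**Illustration.** The documents give no rate for later-onset effects, so the rates here are assumptions. With independent children, the chance that at least one of 22 is affected is 1 − (1 − p)^22:
- p = 2%: 36%
- p = 5%: 68%
- p = 10%: 90%

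So such effects could well occur in a group of this size, and the scheduled questions would not ask about them.

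**The case against.** The strongest reply is that the questionnaire measures tolerability and is not the trial's whole adverse-event system. General reporting of adverse events is commonly left to a full protocol, which is not shown. The discontinuation criteria are not tied to the stimulation window and presuppose that serious events and health changes become known. The Discussion mentions the occurrence of side effects separately from the intensity of sensations. A therapist working with two children is present for the remaining 105 minutes. And nothing in the article says when headache, vertigo or nausea begins.

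Much of this stands, and it rules out several stronger readings that a reader might infer:
- *Later effects go unrecorded, or count as zero in both arms.* The article does not say so; spontaneous reports and staff observation remain possible.
- *Only the skin is looked at again before the next stimulation.* The Design section also has vital signs checked then.
- *The safety aim cannot be met.* Acute sensations, heart rate, SpO2 and skin are covered at every session.
- *The three months to T2 are a gap against the aim.* The abstract's phrase concerns the intervention period, which is two weeks.
- *Active stimulation will look as safe as sham whatever the truth.* That would need later effects to be both common and never volunteered, and the documents show neither.

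What the reply does not remove is the wording. The discontinuation criteria depend on information that no described question seeks, and the promise of careful checking gives no window, schedule or respondent. A fuller protocol might add to these questions, but the article positively limits the ones it describes.

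**Conclusion.** The point holds as a gap in systematic elicitation. Non-skin effects that start after the stimulation window are not asked about, so safety and tolerability over the two weeks are assessed only in part, and the Highlights' claim of proof goes further than the described questions can support. The questions reach 41.7% of training time and, under the weekday assumption, about 4.7% of the time from first to last session.

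How many events this would miss cannot be estimated from the article. That later onset is possible is a judgement about the listed effects, not a stated figure. The conclusion also assumes that no systematic question about the time between sessions exists in a fuller protocol. The efficacy analysis and the sample size are unaffected. The change is worth making because it is cheap and bears directly on a stated aim, but the gap does not invalidate the trial.

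**What to change.** In the safety and tolerability section, keep the post-stimulation questionnaire as it is and add:

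1. The open question and symptom list for the time since the last session, put to child and parent at the pre-stimulation check on days 2 to 10. The list should name headache, vertigo and nausea and carry an item on seizures.
2. The same form at T1 for the time since the last session. A further form at T2 for the time since T1 is optional.
3. A comparison of active and sham on these events, reported separately from acute sensations.

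The Design section's timetable should then match. The two descriptions of the first vital-sign check (before starting, or in the first two minutes) should also be reconciled, so that sites know which contact carries the form.

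If the added questions are not wanted, the abstract and Highlights should limit the safety conclusion to acute effects during stimulation.

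The cost is a few minutes per contact and one more form page, with no new visit. More unrelated background events will be recorded, which the comparison with sham allows for.
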